### Statistical analysis

In general, multi-level regression models (Generalized Linear Mixed Models (GLMM)) with cluster effects (school and class within school) will be used for all statistical analyses. For the primary analysis, a logit model will be used, which will be adjusted for smoking status at baseline, based on the intention to treat (ITT) population. Testing will be hierarchical as described above with an overall level of significance of 5% (two-sided). All further analyses will be considered explorative.

Secondary analysis of the primary endpoint include models with adjustment for smoking status at baseline and other baseline variables in case of relevant imbalances between treatment groups. In addition, missing values will be imputed as sensitivity analyses. A per-protocol (PP) population will be defined and analyzed in a similar manner.

Secondary endpoints will be analyzed within similar frameworks as applicable.

All analyses will be specified in detail in a statistical analysis plan (SAP) which will be finalized prior to data analysis. Data analysis is conducted with the SAS for Windows, Version 9.3 or higher (SAS Institute, Cary, NC, USA) or other software.

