### Study design

This study is a three-armed parallel cluster randomized controlled trial among secondary schools with 7^th^ grade classes. As the unit of randomization schools were randomly assigned using a 1:1:1 ratio and a blocked randomization with variable block length, stratified by school type (Gymnasium vs. integrated secondary school) to one of three intervention groups. The randomization sequence was generated using central computer generated randomization lists and allocation was concealed from participating schools.

Intervention 1:student smoking prevention circuitIntervention 2:student smoking prevention circuit plus parent interventionControl group:student nutrition and physical activity circuit (without smoking prevention)

Given the nature of the intervention, schools and study participants are not blinded to the assigned intervention. However, data analysis of follow-up outcomes will be blinded with regard to the intervention group.

Data collection for each student is conducted at three different time points, including baseline (at the beginning of the 7^th^ grade school year), follow-up 1 (12 month) and follow-up 2 (24 month) (Figure 
1). Prior to baseline data collection one additional visit was performed in all school classes in order to inform students about the study and to distribute participant information and consent forms.

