### Sample size determination

The analysis is following a hierarchical testing procedure. In a first step, intervention 2 (student smoking prevention circuit plus parent intervention) will be compared to the control group with regard to the primary outcome (proportion of regular smokers at 24 months). Only if step 1 is significant at the 5% level (two-sided), will step 2 be tested confirmatively (otherwise all following analyses will be considered explorative). The second step involves two hypotheses: Intervention 1 (student smoking prevention circuit) compared to control; and Intervention 2 compared to Intervention 1, each with regard to the primary outcome. The sample size determination is based on the second step (having a smaller assumed intervention effect, thus requiring a higher sample size than step one) with the two hypotheses tested equally (significance level alpha 0.025 each). Taking into account the cluster design with an assumed intra-cluster correlation coefficient for schools (ICC) of 0.001 and a power of 80%, 15 (14.7 and 13.3 precisely for the two hypotheses) schools (=clusters) are required in each of the three arms to detect a 5% difference in the proportion of regular smokers after two years (assumptions: intervention 1: 30%, intervention 2: 25%, and control group: 35%). Since we assume on average 60 participating students per school, this yields a total of 15 × 3 × 60 = 2700 required students. Assuming a drop-out rate of about 20% this yields a targeted sample size of n = 3375 students to be randomized.

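### The stated primary model omits school type, the factor that stratifies the randomization, so its standard errors are too large if smoking differs by school type

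*Protocol article*

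**What the plan says.** Under Study design, the protocol article describes schools as the unit of randomization, allocated "using a 1:1:1 ratio and a blocked randomization with variable block length". The lists were "stratified by school type (Gymnasium vs. integrated secondary school) to one of three intervention groups". School type is the only stratification factor named.

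Under Statistical analysis, the primary test is set out as follows: "a logit model will be used, which will be adjusted for smoking status at baseline, based on the intention to treat (ITT) population". As the general framework, generalized linear mixed models "with cluster effects (school and class within school) will be used for all statistical analyses". Secondary analyses of the primary endpoint use "adjustment for smoking status at baseline and other baseline variables in case of relevant imbalances between treatment groups". All analyses beyond the hierarchical tests are called explorative.

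Under Objectives, type of school appears only as a possible moderator. Under Sample size determination, the tests are ordered: "Only if step 1 is significant at the 5% level (two-sided), will step 2 be tested confirmatively". Step 1 compares Intervention 2 with control.

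**The concern.** Stratifying by school type keeps the mix of Gymnasien and integrated schools similar across arms, so differences between school types contribute little to the true sampling variation of an arm contrast. A model without school type cannot know this. It counts the difference between school types as ordinary between-school variance, and that variance enters the standard error of every arm contrast. The gain from stratification is made in the design and then not claimed in the analysis.

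All confirmatory claims pass through step 1, so an inflated standard error there can close the gate on the other two primary objectives. The secondary models with further covariates do not repair this, because they are explorative and depend on an observed imbalance.

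**Working it through.** **Inputs from the document.** School ICC 0.001; 60 students per school; 15 schools, hence 900 students, per arm; assumed rates 35% (control), 30% (Intervention 1) and 25% (Intervention 2); step 1 at two-sided 5%. Table 3 gives 15 Gymnasien among 47 schools: 6 of 17, 5 of 16 and 4 of 14 in Intervention 1, Intervention 2 and control.

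**Assumption.** The smoking gap d between school types is not given. It is varied from 0 to 20 percentage points.

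**The plan's own figures.** The Gymnasium shares reproduce: 525/1142 = 46.0%, 394/980 = 40.2%, 254/679 = 37.4%. So do 15 × 3 × 60 = 2700 and 2700/0.8 = 3375. The planned design effect is 1 + 59 × 0.001 = 1.059. (The stated 14.7 and 13.3 schools per arm do not reproduce from the stated inputs. That is a separate point, and nothing below depends on it.)

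**1. Variance that school type adds when omitted.** With w = 15/47, w(1 − w) = 0.2173. At an overall rate of 30%, the added ICC is 0.2173 d² / (0.3 × 0.7). The standard-error ratio, without versus with school type, is the square root of (design effect without / 1.059).

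| d (points) | ICC without school type | Design effect | SE ratio |
|---|---|---|---|
| 0 | 0.001 | 1.059 | 1.00 |
| 5 | 0.0036 | 1.212 | 1.07 |
| 10 | 0.0113 | 1.669 | 1.26 |
| 15 | 0.0243 | 2.433 | 1.52 |
| 20 | 0.0424 | 3.501 | 1.82 |

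**2. The limit set by the plan's ICC.** If 0.001 is the total school ICC, school type included, the largest possible gap is √(0.001 × 0.21 / 0.2173) = 0.031, or 3.1 points. The standard error is then inflated by at most √1.059 = 1.029, about 3%.

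**3. Step 1 power at the planned size.** With school type, SE = √((0.35 × 0.65 + 0.25 × 0.75) × 1.059 / 900) = 0.0221. Without it, the reported SE is 0.0278 at d = 10 and 0.0402 at d = 20, but under stratification the estimate still varies with an SD of about 0.0221. Power without school type is therefore Φ((0.10 − 1.96 × 0.0278)/0.0221) = 98% at d = 10 and Φ((0.10 − 1.96 × 0.0402)/0.0221) = 83% at d = 20, against 99.5% with it. Putting the inflated design effect into the usual power formula gives 95% and 70%. That overstates the loss at this size, because it treats the inflated SE as real sampling variation.

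**4. Step 1 power at the achieved size.** Two school-level simulations used the Table 3 school numbers, 80% retention and a residual ICC of 0.001, without baseline smoking. At d = 20, power was 72% without and 94% with school type in one, and 66% and 97% in the other. At d = 10, the SE ratio was 0.0316/0.0266 = 1.19 and 0.028/0.023 = 1.22.

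**5. The planned type of model.** A logit mixed model with a school random intercept and baseline smoking as covariate was simulated on the Table 3 schools (80% retention, 300 runs per scenario, no class effect; assumed baseline smoking 5% in Gymnasien and 10% in integrated schools). A school-type log odds ratio of −0.5 or −1.0 around 30% corresponds to a gap of about 10 or 19 points. Results for Intervention 2 versus control, no true effect, schools re-randomized within type:

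| Log OR of type | Empirical SD (without school type) | Mean SE without | Mean SE with |
|---|---|---|---|
| −0.5 | 0.126 | 0.148 | 0.122 |
| −1.0 | 0.121 | 0.214 | 0.125 |

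Without school type, null rejection at nominal 5% was 2 to 3% at −0.5 and under 1% at −1.0; with it, about 4 to 5%. Under a treatment log odds ratio of −0.48 (the 35% versus 25% contrast) and a type effect of −1.0, power was 75% without and 97% with school type. With no type effect the two models agreed.

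**6. Realized imbalance.** The shift is the difference in Gymnasium share times d.
- Intervention 1 versus control: 46.0 − 37.4 = 8.6 points weighted by student, 6/17 − 4/14 = 6.7 weighted by school. This gives 0.7 to 0.9 points at d = 10 and 1.3 to 1.7 at d = 20, against an assumed effect of 5.
- Intervention 2 versus control: 2.8 and 2.7 points. This gives about 0.3 at d = 10 and 0.5 to 0.6 at d = 20, against an assumed effect of 10.

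**The case against.** Four points can be made on the other side.

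- **The plan's ICC leaves no room for a large effect.** Read as the total school ICC, 0.001 allows a gap of about 3 points and a loss that hardly matters. This stands as a limit on what can be claimed. But the document does not say whether 0.001 includes school type, and a larger gap would reveal itself only in the data.
- **Baseline smoking is in the model.** It may carry part of any school-type difference. That is fair, although the mixed-model simulation included it and the standard error was still inflated.
- **Detail is deferred.** The article says "All analyses will be specified in detail in a statistical analysis plan (SAP) which will be finalized prior to data analysis", and it does not state that baseline smoking is the only covariate. However, it names the primary adjustment and sends other baseline variables to secondary models. A later plan that followed this text would leave school type out.
- **The unequal Gymnasium shares suggest bias.** A reader might infer that omitting school type biases the contrasts. The document does not support this. Stratified randomization balances school type in expectation; the student shares reflect school sizes and which schools remained, including the withdrawal of two control schools after allocation. This is a modest realized imbalance, partly addressed by the planned secondary models.

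**Conclusion.** The point holds as one of efficiency. The design stratifies by school type and the stated primary model does not use it. If smoking differs by school type, reported standard errors are too large and the confirmatory tests conservative. The mechanism is certain; its size is conditional on the gap:

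- **0 to 3 points:** negligible.
- **10 points:** standard errors about 20 to 26% too large; step 1 power falls only slightly.
- **20 points:** step 1 power falls from above 90% to about 66 to 72% in the school-level simulations at the achieved size. The loss is smaller at the planned 900 students per arm.

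Neither systematic bias nor inflated type I error follows. What stays unadjusted in the primary test is a chance imbalance. If Gymnasium students smoke less, it would flatter Intervention 1 against control by less than 2 points even at a 20-point gap, and would work slightly against Intervention 2 in its comparison with Intervention 1. The figures rest on the assumed gap, and the achieved-size power figures also on 80% retention. Only the mixed-model simulation included baseline smoking, and it left out the class effect.

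**What to change.** Before data analysis, write the primary model as a logit mixed model with fixed effects for arm, baseline smoking status and school type (the stratification factor), and random effects for school and class within school. Include school type unconditionally, not only if an imbalance is seen. Recruitment wave is not named as a stratification factor and is not needed for this purpose.

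The cost is one parameter. School type is known for every school, and with no school-type effect the two models gave practically the same results. The odds ratio becomes conditional on school type as well, which changes its meaning slightly and should be stated when it is reported.

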## Results

### Recruitment process and distribution of participating schools and students

Schools, school classes and study participants were recruited over a period of two school years. Out of all 214 secondary schools in Berlin that were approached in 2010, a total of 49 secondary schools were enrolled over two recruitment waves and randomized. Two schools withdrew despite their initial commitment after being randomized to control group, leaving a total of 47 participating schools. During the school year 2010/11 (wave 1) 32 schools were enrolled. Further 15 schools were enrolled during the school year 2011/12 (wave 2)). For details of the school and participant recruitment process see Figure 
2. Schools were recruited from all 12 districts of the city state of Berlin (s. Figure 
3). With regard to the school type, 32 are considered integrated secondary schools while 15 schools are high schools (“Gymnasien”).

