## Background

The hazardous health effects of smoking and second hand smoke are well known. Although smoking rates in many industrialized countries have declined over past decades, absolute number of smokers is increasing and so is the absolute mortality attributable to smoking
[1–3]. Tobacco use among children and adolescents in many industrialized countries has decreased in recent years, including Germany
[4–7]. However, compared to other western countries, smoking rates in Germany are still relatively high which is cause for concern, given the numerous detrimental health effects of smoking
[8].

The majority of adult smokers initiate this unhealthy behavior during adolescence, and almost every adult who smokes started smoking before the age of 26
[9]. Targeting children and adolescents is therefore the most appropriate approach to prevent smoking initiation in the first place. School-based prevention strategies have traditionally been an important approach to smoking prevention in children and youths. Particular advantages are that schools offer an almost universal reach of children and youths. In addition, educational strategies fit mutually with schools’ role
[10]. However, the effectiveness of such strategies has been mixed and systematic reviews reported limited evidence of the long-term effectiveness of school-based smoking prevention strategies
[10, 11].

Parents have a strong influence on their children’s smoking behavior in various ways. For instance, children of parents who smoke are more likely to smoke
[12]. Moreover, parental anti-smoking attitudes and rules have shown to be associated with children’s smoking behavior, irrespective of their own smoking behavior
[13–15]. Given the at best modest long-term effectiveness of behavioral smoking prevention strategies
[10]. and the important role of parents in shaping children’s smoking behavior, parental and family-based intervention strategies have been added to student centered school-based smoking prevention strategies. However, only a limited number of methodologically rigorous studies have investigated the effectiveness of family or parental approaches to smoking prevention and while some reported favorable outcomes, others reported less positive findings
[16–19]. Recent systematic reviews of the evidence have suggested that studies incorporating parental or family components could indeed beneficially influence smoking behavior in children and adolescents

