## Discussion

The BEST-Prevention study is among the largest randomized controlled trials in Germany that investigates the effectiveness of smoking prevention strategies among adolescents
[10]. It was designed to address important and unresolved issues in the context of behavioral smoking prevention strategies. Findings will be of importance for a number of reasons: Firstly, the BEST-Prevention study targets specific intervention components and addresses the additional effectiveness of a feasible parental smoking prevention strategy to reduce smoking rates among adolescents, which few studies have done so far
[11, 20]. Secondly, it targets adolescents at increased risk of smoking due to their diverse background and their residence in a large metropolitan area in Germany. Thirdly, this study assesses the long-term effectiveness of a smoking prevention intervention.

Despite recruitment challenges due to the implementation of a school reform in Berlin in 2010, which reduced the number of potentially eligible schools by about 50%, the targeted number of 45 schools and 161 school classes was achieved or even exceeded. However, with 3023 students meeting all selection criteria, the estimated sample size was not fully met.

Although our study did not aim to enroll a representative population of 7^th^ graders in Berlin we were able to recruit schools and students from all 12 districts of the city. This ensures that schools and students are located in districts and neighborhoods with diverse characteristics and SES. While we recruited schools, school classes and students from all these districts, the distribution of those does not fully reflect the general distribution across the city of Berlin. For instance, certain districts are overrepresented in terms of the relative number of schools and students enrolled, while others underrepresented. In terms of the type of school, there are 121 integrated secondary schools and 93 “Gymnasien” in Berlin. Within the BEST-Prevention study we enrolled 32 integrated secondary schools and 15 Gymnasien, reflecting a somewhat different distribution. Our population based sample in a major metropolitan area in Germany and its diversity will offer the opportunity to investigate the impact of various individual family characteristics, as well as neighborhood SES on smoking and other health behaviors. This will make findings highly relevant to populations which are frequently not adequately reached through prevention efforts.

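### Recruitment wave (32 schools in 2010/11, 15 in 2011/12) is not named in the primary model; pre-specifying it is an optional, nearly free gain in precision, not a correction of an error

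*Protocol article*

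**What the plan says.** All references are to the protocol article.

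- **Recruitment** (Recruitment process and distribution of participating schools and students): "a total of 49 secondary schools were enrolled over two recruitment waves and randomized". After two control schools withdrew, 47 remained. "During the school year 2010/11 (wave 1) 32 schools were enrolled", and "Further 15 schools were enrolled during the school year 2011/12 (wave 2").
- **Allocation** (Study design): 1:1:1 in blocks of variable length, "stratified by school type (Gymnasium vs. integrated secondary school) to one of three intervention groups". Wave is not named as a stratification factor.
- **Primary model** (Statistical analysis): a logit mixed model with effects for school and for class within school, "which will be adjusted for smoking status at baseline, based on the intention to treat (ITT) population". The same section puts adjustment for other baseline variables into secondary analyses, to be used if relevant imbalances appear. It treats everything beyond the hierarchical tests as exploratory and leaves full detail to an SAP to be finalised before data analysis.
- **Context**: the Background states that "Tobacco use among children and adolescents in many industrialized countries has decreased in recent years, including Germany". The Discussion mentions "the implementation of a school reform in Berlin in 2010".

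**The concern.** The two cohorts contain different students. Baseline is at the start of 7th grade, so their 24-month assessments lie about one school year apart. If smoking uptake differed between those periods, schools would differ systematically by wave. A model without a wave term counts that difference as unexplained variation between schools.

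All three confirmatory comparisons are between schools, so removable between-school variance enlarges their standard errors. Wave is known for every school before any outcome is seen, so its inclusion need not depend on a check for imbalance. What is at stake is precision, chiefly in the two step-2 tests, each run at a two-sided 0.025.

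**Working it through.** **Inputs from the document.** 32 and 15 schools (Recruitment process). School ICC 0.001, 60 students per school, 80% power, alpha 0.025 for each step-2 hypothesis, and rates of 35%, 30% and 25% (Sample size determination).

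**Assumption.** The wave difference d in 24-month prevalence is not given. I use 1, 2, 3 and 5 percentage points around a prevalence of 30%, so p(1 − p) = 0.21. The calculation is on the prevalence scale, as an approximation to the logit model.

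**1. The plan's own figures.** The planning design effect is 1 + 59 × 0.001 = 1.059. For 35% v 30%, schools per arm = (0.35 × 0.65 + 0.30 × 0.70) × (2.241 + 0.842)² / 0.05² × 1.059 / 60 = 29.4. For 30% v 25% the same formula gives 26.7. The stated 14.7 and 13.3 are half of these and were not reproduced as per-arm numbers. That is a separate matter. Here it means that the 80% below is only a nominal reference.

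**2. Variance added by leaving wave out.** With w = 15/47, w(1 − w) = (15/47)(32/47) = 0.217.

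- Added ICC = 0.217 × d² / 0.21
- Design effect = 1 + 59 × (0.001 + added ICC)
- Power = Φ(3.083 / √ratio − 2.241), where ratio = design effect / 1.059 and 3.083 = 2.241 + 0.842

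| d (points) | Added ICC | Design effect | Ratio | Power, from nominal 80% |
|---|---|---|---|---|
| 1 | 0.0001 | 1.065 | 1.006 | about 79.8% |
| 2 | 0.0004 | 1.083 | 1.023 | 79.0% |
| 3 | 0.0009 | 1.114 | 1.052 | 77.8% |
| 5 | 0.0026 | 1.212 | 1.144 | about 74% |

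**3. The same loss at 15 schools of 60 per arm.** From the stated inputs, step-2 power without any wave effect is about 48% (35% v 30%) and 53% (30% v 25%). With d = 3 it is about 46% and 50%. With d = 5 it is about 43% and 46%.

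**4. Step 1 (35% v 25%, alpha 0.05, 15 schools per arm).** Power is 99.5% with no wave effect and 98.8% with d = 5.

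**5. Type I error.** School-level two-sided 5% tests were simulated with 15 v 15 schools, 20 of the 30 in wave 1, a 30% rate, ICC 0.001 and 10,000 runs per setting. The Monte Carlo standard error is √(0.05 × 0.95 / 10,000) = 0.002.

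| d (points) | No wave term | With wave term |
|---|---|---|
| 0 | 0.049 | 0.051 |
| 5 | 0.052 | 0.053 |
| 10 | 0.052 | 0.053 |

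Leaving wave out does not inflate the error rate.

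**The case against.** **The SAP may already include wave.** The article is a summary and defers detail to an SAP that is not shown. A reader might infer that the final primary model has no wave term, but the document cannot establish that. Still, the article is not silent. It names the primary adjustment and assigns other baseline variables to imbalance-triggered secondary models. As described, wave would enter only there.

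**Nothing is invalid.** A reader might infer that pooling cohorts a year apart biases the comparison. It does not. Schools in both waves were randomised, and each student is followed for 24 months from their own baseline. A chance imbalance in wave between arms is already covered by the school effect and its standard error. This objection stands in full.

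**The size is assumed and probably overstated.** At 1 to 2 points the loss is about one power point or less. Baseline-smoking adjustment would absorb part of any cohort difference, though not necessarily differences in later uptake. The planning ICC is not said to exclude cohort differences. At d = 3 the added ICC is about as large as the whole planning ICC, but mainly because that ICC is so small. With an assumed ICC of 0.02, the same d raises the variance by only (2.18 + 0.055) / 2.18, about 2.5%.

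**The context does not show a wave difference.** The Background reports a general decline with no annual rate. The Discussion mentions the school reform only as an obstacle to recruitment. It dates from 2010, the year in which all 214 schools were approached, and is not linked to smoking. A reader might take it as evidence that the waves differ, but the text does not support that.

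**Conclusion.** The point holds as a low-severity efficiency suggestion. The article documents two annual cohorts and a primary model whose only named covariate is baseline smoking status. A wave difference not explained by that covariate would cost precision, with no bias in expectation and no excess false positives.

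Under the assumed differences of 1 to 5 points, the cost in the step-2 tests runs from a fraction of a power point to about 6 points, as an upper estimate that ignores baseline-smoking adjustment. Step 1 barely changes. The case for acting is that the step-2 tests have little power to spare and the remedy costs almost nothing. It does not rest on any demonstrated difference between the waves.

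**What to change.** Optional: before data analysis, pre-specify recruitment wave (2010/11 v 2011/12) in the SAP as a fixed school-level term in the primary mixed model, whether or not an imbalance is observed.

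The cost is one line of SAP wording and one between-school degree of freedom out of about 44 (47 schools less 3 arms). If there is no wave effect, the loss is negligible. No new data are needed, because wave is known for every school.
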